### Measures

Primary outcome measures, secondary outcome measures, outcomes regarding feasibility of implementation, and measures of moderating variables and control variables can be distinguished in this study. The instruments include several questionnaires for parents and one observation measure for parent and child at each assessment, several questionnaires for the VIPP-V intervention worker at pretest and post-test and one questionnaire for the early intervention worker who provides care-as-usual in the family at pretest.

After the start of the trial changes were made in the designation of primary and secondary outcome measures. To increase feasibility of the study, in the early stages of the trial the original proposal was changed so that parental sensitivity and quality of parent-child interaction is now coded with all National Institute of Child Health and Human Development Scales (NICHD-scales), and parental self-efficacy and parenting stress are secondary outcome measures rather than primary outcome measures.

### Primary outcome measures

The main research question of this study is whether parents of a child with a visual or visual-and-intellectual disability will benefit from participating in VIPP-V in terms of higher parental sensitivity and better parent-child interaction quality compared to receiving care-as-usual only.

#### Parental sensitivity and quality of parent-child interaction

At pretest, post-test and follow-up the Three Boxes-procedure [22, 23] will be used to observe parental sensitivity and quality of parent-child interaction. Since all assessments take place during home-visits instead of in the lab, the originally used boxes in the Three Boxes-procedure were changed for bags in this study for ease of transportation. For this procedure parent-child dyads are offered three bags with toys. Small adaptations have been made to the originally used toys to make the play sets also appropriate for children with visual disabilities. The first bag contains a tactile reading book (different books are used for younger children (1–2 years) and older children (3–4 years)); a play tea set is in the second bag (this set consists of tea cups of different materials: for example a metal tea cup, a wooden tea cup and a plastic tea cup, so blind children will also have enough possibilities for exploration; the tea set for older children consists of more items); a set of Duplo building blocks is in the third bag (more blocks are in the play set for older children). Parents are instructed to play with their child with the toys in the three bags in a specified order (each bag is numbered 1–3). The **National Institute of Child Health and Human Development Scales (NICHD-scales)** will be used to code parental sensitivity and quality of parent-child interaction in the Three Boxes-procedure [24]. These scales will be scored on a 7-point Likert-scale, ranging from *“very low (1)”* to “*very high (7)”* Coders will be trained by the fourth author ([name]. [name]), who has established reliability in previous studies [25, 26]. Tapes will be randomly assigned to coders, and coders will be blind to condition and assessment. In a previous study Cronbach’s alpha for a composite parental sensitivity measure (sum of scales) ranged from 0.70 to 0.78, and high intercoder reliability was achieved, ranging from 0.83 to 0.87 [22].

### Secondary outcomes

Secondary outcome measures focus on whether parents of a child with a visual or visual-and-intellectual disability will benefit from participating in VIPP-V in terms of higher parental self-efficacy and lower parenting stress compared to receiving care-as-usual only.

#### Parental self-efficacy

The **Self-efficacy in the Nurturing Role questionnaire (SENR)** [27] will be administered to parents at pretest, post-test and follow-up to measure parental self-efficacy. This questionnaire consists of 16 items, which can be rated on a 7-point scale ranging from *“not at all applicable to me (1)”* to *“totally applicable to me (7).”* Items capture parents’ perceptions of their competence on basic skills required in taking care of their child. Items were modified slightly to be appropriate for parents parenting children aged 1–5 years, instead of infants. Examples of items are: *“I feel competent in my role as a parent”* and *“Touching, holding and being affectionate with my child is comfortable and pleasurable for me.”* In previous research with mothers of infants internal reliability was high, with a Cronbach’s alpha ranging from 0.86 to 0.89 [28].

#### Parenting stress

At pretest, post-test and follow-up parents will be asked to fill out the shortened Dutch version of the **Parenting Stress Index (PSI)** [29, 30] to measure the overall stress experienced in parenting. This questionnaire consists of 25 items divided in a scale for child-related parenting stress and a scale for parent-related parenting stress. An example of an item regarding child-related parenting stress is: *“My child cries or fusses more often than other children*,*”* and an example of an item regarding parent-related parenting stress is: *“I often feel that I cannot handle things.”* Parents are asked to answer on a 6-point scale, ranging from *“totally disagree (1)”* to *“totally agree (6).”* Internal consistency in previous research ranged from 0.92 to 0.95 and validity seems acceptable [30].

### Outcomes regarding feasibility of implementation

If study-results show VIPP-V to be an effective intervention a second goal of this study is to assess the feasibility of implementing VIPP-V in the regular care provided by early intervention workers at Royal Dutch Visio and Bartiméus.

#### Experiences of early intervention workers with VIPP-V during early intervention

An adaptation of the **Social Validity Scale** [31, 32] will be administered at post-test to VIPP-V intervention workers to assess the desirability, applicability, clarity, efficiency and burden of integrating VIPP-V in the current range of care provided by Royal Dutch Visio and Bartiméus. This questionnaire consists of 35 questions and 18 statements. The questions cover four topics (evaluation of the ideas behind the VIPP-V intervention, evaluation of offering VIPP-V in the participating family, subjective evaluation of the effectiveness of VIPP-V in the participating family and evaluation of completing the different questionnaires) and can be answered on a 5-point scale. The statements are formulated more generally and focus on three topics (application of acquired VIPP-V skills, subjective evaluation of the effectiveness of VIPP-V, usefulness of VIPP-V) and can be answered on a 3-point scale.

### Measures of moderating variables

Data will be gathered regarding demographic variables, child’s developmental age, working alliance between parent and VIPP-V intervention worker and empathy of the VIPP-V intervention worker to determine whether there are certain subgroups for whom or circumstances under which VIPP-V is most effective.

#### Demographic variables

Before pretest, parents complete a 14-item self-designed demographic questionnaire. Questions are included regarding age and gender of the parent, child and other family members, cultural and socio-economic background, health of parents, nature and severity of the disability of the child, medical background of the child, use of medication of the child and possible disabilities of other family members. This questionnaire is administered before pretest, because parents who have visual or auditory disabilities themselves will be included as extra case studies, children with a severe intellectual disability (developmental age below nine months) will be excluded from participation and randomization will be done stratified on the chronological age of the child (to control for the number of years the parent has had experience in interacting with the child).

#### Child’s developmental age

For parents it will sometimes be difficult to assess the developmental age of their child correctly on the demographic variables questionnaire. Therefore, the early intervention worker who provides care-as-usual in the family will be asked to fill out the Dutch screening version of the **Vineland Adaptive Behavior Scales (VABS)** [33, 34] around pretest to obtain a more objective measure for children’s developmental age. If an early intervention worker is not available, a professional who is otherwise closely involved with the child, such as a teacher, will be asked to fill out this questionnaire. This screening instrument consists of 93 items to measure children’s adaptive behavior on four domains: Communication, Daily Living Skills, Socialization and Motor Skills. A previous study on the psychometric properties of this Dutch translation administered to parents showed good validity, excellent internal consistency (Cronbach’s alpha = 0.99) and test-retest reliability (Intraclass Correlation Coefficient (ICC) = 0.95) [35].

#### Working alliance between parent and VIPP-V intervention worker

The therapeutic alliance has been found to predict treatment outcomes and seems an important aspect of successful intervention [36]. Therefore, the Dutch translation of the short version of the **Working Alliance Inventory (WAI)** [37–40] will be administered to both the parent and the VIPP-V intervention worker at post-test to assess their feelings of working alliance. This questionnaire consists of 12 items, measuring general alliance as well as three specific aspects of alliance (Bond, Goals and Tasks). An examples of an item is: *“We* (the parent and VIPP-V intervention worker) *have established a good understanding of the kind of changes that would be good for me and my child.”* Items are scores on a 5-point scale, ranging from *“never (1)”* to *“always (5).”* Validity and reliability of the original English version has been demonstrated to be good [37]. During VIPP-V the VIPP-V intervention worker also fills out a notebook and profile of the participating parent after every home-visit to report on the course of the visit, the collaboration with the parent and the progress the parent has made between visits. This notebook and profile will be used to support the data gathered on the WAI.

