**Methods/Design:**

A randomized controlled trial (RCT) will be conducted to assess the effectiveness of the adapted intervention VIPP-V (Video-feedback Intervention to promote Positive Parenting in parents of children with Visual or visual-and-intellectual disabilities). Parent-child dyads will be randomized into two groups: 50 dyads will receive VIPP-V in combination with care-as-usual and 50 dyads will receive care-as-usual. Families with a child (1–5 years of age) with a visual or visual-and-intellectual disability will be recruited for participation in the study. Primary outcome measures are parental sensitivity and the quality of parent-child interaction. Secondary outcome measures are parental self-efficacy, and parenting stress. To assess feasibility of implementation of the intervention the experiences of early intervention workers with regard to using VIPP-V are assessed. Moderator variables are the child’s developmental age, working alliance between parent and VIPP-V intervention worker and empathy of the VIPP-V intervention worker. Data will be collected approximately one week before the intervention starts (T1), one week (T2) and three months (T3) after the intervention. Parent-child dyads in the care-as-usual-only condition will be assessed at the same time points. Both intention-to-treat and completer analyses will be performed.

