### Trial objective

In the present study we will examine the effectiveness of an attachment-based video-feedback parenting intervention for parents of children with a visual or visual-and-intellectual disability (VIPP-V) by use of a randomized controlled trial (RCT) with two groups: one group will receive VIPP-V in combination with care-as-usual and one group will receive care-as-usual only. Effectiveness is measured in terms of improved parental sensitivity, parent-child interaction quality, parental self-efficacy and decreased parenting stress. Potential moderating variables will be investigated in order to identify predictors of effectiveness. A secondary goal of the study is to assess the feasibility of implementing VIPP-V in regular care and prepare the field for broad-scale implementation if the new intervention is effective.

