### Procedure

To recruit families for participation in the study Royal Dutch Visio and Bartiméus will send an information package, including a letter, brochure and consent form developed by the researchers, as well as a cover letter from the organization to all families in their databases who meet the inclusion criteria. In addition to this broad approach, also all early intervention workers are asked to personally inform the families in their caseload who are eligible for participation about the study. If families decide to participate in the study, they sign a consent form and fill out a demographic questionnaire. When they return these forms to the university, their personal data becomes known to the researchers. Families who are approached for participation, but do not wish to participate in the study, remain anonymous to the researchers. If parents have questions regarding the study they can phone or email one of the eight VIPP-V coaches working at Royal Dutch Visio and Bartiméus or one of the researchers.

After informed consent and demographics are obtained, families are enrolled in a block of 16–18 families. In both organizations three blocks of 16–18 families will be formed, to include a total of 100 families in the study. When the maximum number of families for the block is reached, families will be randomized, and a few weeks later the intervention will start. The intervention will start on three different occasions over the year, so each intervention worker provides VIPP-V to approximately one family at a time. After randomization families are informed in which condition they will participate through a letter by the research team. A research assistant makes an appointment with the family for the pretest assessment (T1). After the pretest the intervention starts. After about five months the intervention is finished and a post-test takes place. Three months later an appointment is made for the follow-up assessment. Families participating in the control condition will be assessed at the same time points (see Fig. 1).

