### Data analysis

All analyses will be done using the software program SPSS (version 21.0). Baseline characteristics will be described in descriptive analyses. Before analyzing, differences in baseline characteristics between the experimental and control condition will be checked. If differences are found, they will be reported and controlled for in further analyses. Before analyzing, outliers will be checked and winsorized if necessary. For analyses of the primary and secondary outcome measures of the study (parental sensitivity, parent-child interaction quality, parental self-efficacy and parenting stress) ANOVA repeated measures or multilevel analyses will be used, depending on the level of clustering in the data. Intention-to-treat and completer analyses will be performed. The primary and secondary outcome measures of families in the experimental condition will be compared with their own scores on a previous assessment, as well as with scores of families in the control condition at the same assessment. Change over time from pretest to post-test and from pretest to follow-up in parental sensitivity, quality of parent-child interaction, parental self-efficacy and parenting stress will be assessed in the experimental group, and compared with the control group. Results will be described as rates of change. The outcome measure regarding feasibility of the intervention ‘Experiences of VIPP-V intervention workers with VIPP-V during early intervention’ will be reported in descriptive analyses. Multivariate regression analysis or multilevel moderator analyses will be performed with different predictors (demographic variables, child’s developmental age, working alliance between parent and VIPP-V intervention worker, empathy of the VIPP-V intervention worker) to study for whom and under which circumstances VIPP-V intervention is most effective. For these analyses only the data of the families in the VIPP-V intervention condition will be used.

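### Working alliance is used as a predictor of VIPP-V effectiveness but is measured only at post-test, so its association with change from pretest is open to reverse causation

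*Protocol article*

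**What the plan says.** The abstract lists alliance among the moderators: "Moderator variables are the child’s developmental age, working alliance between parent and VIPP-V intervention worker and empathy of the VIPP-V intervention worker". The Trial objective section gives the purpose: "Potential moderating variables will be investigated in order to identify predictors of effectiveness". The section on measures of moderating variables says the data serve "to determine whether there are certain subgroups for whom or circumstances under which VIPP-V is most effective". The Data analysis section enters alliance with the other predictors "to study for whom and under which circumstances VIPP-V intervention is most effective", and adds: "For these analyses only the data of the families in the VIPP-V intervention condition will be used".

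The section on working alliance fixes the timing. The short WAI "will be administered to both the parent and the VIPP-V intervention worker at post-test to assess their feelings of working alliance"; no other WAI administration is described. Under Procedure, "After about five months the intervention is finished and a post-test takes place". The primary outcome is taken at that same assessment: "At pretest, post-test and follow-up the Three Boxes-procedure [22, 23] will be used to observe parental sensitivity and quality of parent-child interaction". The parent also completes the self-efficacy and parenting stress questionnaires then.

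The intervention worker keeps a notebook and profile after each home-visit, covering the course of the visit, the collaboration and the parent's progress. The article gives these records a supporting role to the WAI.

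The Data analysis section plans two change contrasts, pretest to post-test and pretest to follow-up.

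**The concern.** The plan's question about alliance has a direction: does VIPP-V work better where parent and worker get on well? Answering it needs a measure of alliance taken before the change it is meant to explain. The only WAI score is taken once the intervention has ended, when parent and worker both have an impression of how it went. A high score could have helped the improvement, or could reflect it.

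The article makes the second route plausible. At the same post-test the worker also completes the Social Validity Scale, which includes a subjective rating of how effective VIPP-V was in that family. The parent who rates alliance also rates self-efficacy and stress.

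At stake is a practical conclusion. Services could be told that good alliance makes VIPP-V more effective, from data that cannot separate this from alliance being rated higher where VIPP-V went well. The moderator analyses are not incidental: the sample size section says 58 families suffice for the main question and gives moderator analyses as the reason for aiming at 100.

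**Working it through.** **Step 1. When each moderator is measured, from the Measures sections**

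| Moderator | Timing | Measured before the T2 outcome? |
|---|---|---|
| Demographic variables | before pretest | yes |
| Child's developmental age | around pretest | yes |
| Worker empathy | pretest and post-test | yes, at pretest |
| Working alliance (WAI) | post-test only | no |

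Alliance cannot be rated before the relationship exists, so a pretest score is not expected. It could be rated during the intervention, but the only such record is the notebook. That is completed by the worker alone and also records the parent's progress, so it does not separate alliance from improvement.

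**Step 2. The T2 WAI against each contrast**

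- T1–T2 change (planned): all of it occurs before or at the WAI.
- T1–T3 change (planned): this equals T1–T2 change plus T2–T3 change. The first part precedes the WAI and the second follows it.
- T2–T3 change (not among the two named contrasts): all of it follows the WAI.

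**Step 3. How often reverse influence alone would look like a predictor**

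The article gives no figure for this, so there is none to reproduce. Inputs from the article: 50 families in the VIPP-V arm (abstract), that arm only (Data analysis) and alpha 0.05 (sample size section, applied here as a two-sided test).

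Assumptions, not taken from the article: alliance has no effect on outcome; perceived success gives the T2 WAI a correlation r of 0.2, 0.3 or 0.4 with T1–T2 change; the two change scores correlate 0.5; and the WAI is related to T1–T3 change only through T1–T2 change, so its correlation with T1–T3 change is 0.5 × r.

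Fisher z approximation: z = atanh(r) × √(50 − 3) = atanh(r) × 6.856. The chance of a significant result is Φ(z − 1.96) + Φ(−z − 1.96).

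| r with T1–T2 change | z | Chance | Simulated | Implied r with T1–T3 change | z | Chance | Simulated |
|---|---|---|---|---|---|---|---|
| 0.2 | 1.39 | 28% | 28.7% | 0.10 | 0.69 | 11% | 11.0% |
| 0.3 | 2.12 | 56% | 56.4% | 0.15 | 1.04 | 18% | 17.8% |
| 0.4 | 2.90 | 83% | 83.5% | 0.20 | 1.39 | 28% | 29.1% |

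The simulated columns come from 20,000 runs with n = 50 and a t-test of the correlation. With r = 0 the same simulation rejected in 5.1% (T1–T2) and 5.0% (T1–T3) of runs, as it should.

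**The case against.** Several counter-arguments have force.

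- **The T2 WAI precedes T3.** A reader might infer that a post-test score can never serve as a predictor. The documents do not support that: follow-up is three months later, and the T2 WAI is correctly ordered for T2–T3 change. For T1–T3 change the problem is reduced but not removed.
- **The primary outcome is coded blind.** Coders know neither condition nor assessment, and the article does not suggest that parents or workers see the codes before rating alliance. Reverse influence then requires their impression of success to track the coded change. That is less direct than for self-efficacy and stress, where the parent rates both sides. Blind coding removes rater bias but does not stop real improvement from raising the alliance rating.
- **The percentages rest on assumed correlations.** This is so. They are the power to detect an association assumed to exist, and it would be wrong to read them as inflated type I error of the correlation test. The association would be real; only its interpretation as a predictor of effectiveness would be wrong.
- **Drop-out.** A reader might infer that poor-alliance families are lost before T2 and the range of scores is cut. The article gives no drop-out figure and no link with alliance, and it plans post-tests, where possible, for families who leave the intervention. This remains speculation and forms no part of the point.
- **An end-of-treatment WAI covers the whole relationship.** That is a reason to keep it, but it does not put alliance before improvement.
- **Consequences are limited.** Alliance is one of several moderators, appears in neither main hypothesis, and leaves the comparison of the two conditions untouched. This sets the weight of the point without removing it.

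**Conclusion.** The point stands in a bounded form. The article assigns alliance a predictive role but measures it only after the intervention, alongside the T2 outcomes. Its association with T1–T2 change cannot show direction, and its association with T1–T3 change is affected to a smaller degree. The ambiguity is greatest for parental self-efficacy and parenting stress, and smaller for observed sensitivity and interaction quality. The worker's notebook does not resolve it.

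The calculation shows that modest reverse influence would be enough to produce a nominal predictor in many trials of this size, and that T1–T3 change is less exposed. Its size depends wholly on the assumed correlations, so it illustrates the risk and does not estimate it for this trial. The main treatment comparison is not in question. The change is worth making because it alters what may be concluded about alliance at little cost.

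**What to change.** 1. **Reporting, for all families.** Report the association of the T2 WAI with T1–T2 and T1–T3 change as a process correlate, not as a predictor or moderator of effectiveness. Use the T2 WAI as a predictor only for T2–T3 change. This needs no new data.
2. **Measurement, for blocks not yet started.** Give the 12-item WAI to parent and worker early in VIPP-V, for example after home-visit 3. Use that score as the predictor and keep the post-test WAI.

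The cost of the second step is one extra short form for parent and worker and a minor ethics amendment. An early score reflects only the first feedback sessions: Table 1 shows that discussion of the recordings starts at home-visit 2, so after home-visit 3 there have been two. Because data collection is already in progress, few families may have an early score, and the article does not say how many blocks remain. If none remain, the first step alone is sufficient.
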